---

---

| 3 | 3.1 Overall Design                         | The participants will be recruited from the Chinese PLA General Hospital, Harbin Medical University Affiliated Cancer Hospital, and Hainan Provincial People's Hospital.                                                                                                                                                               | The participants will be recruited from the Chinese PLA General Hospital, Harbin Medical University Affiliated Tumor Hospital, the First Affiliated Hospital of Zhejiang University School of Medicine, the First Affiliated Hospital of Anhui Medical University, the First Affiliated Hospital of Xinjiang Medical University, and Hainan Provincial People's Hospital. |
| 4 | 3.4.4 Operation process of the telesurgery | In the telesurgery group, the first surgeon activates the main console and the teleconference subsystem on the surgeon's side, and the patient's side activated the teleconference system, surgical cart and the backup console of the surgery robot. Telesurgery technical teams in Beijing and Harbin/Haikou are responsible for the | In the telesurgery group, the first surgeon activates the main console and the teleconference subsystem on the surgeon's side, and the patient's side activated the teleconference system, surgical cart and the backup console of the surgery robot. Telesurgery technical teams in Beijing and Urumqi/Harbin/Hangzhou/Hefei/Haikou are responsible for the              |

|   |        |                                                                                                                                                                                                                                                                                                                                                                                                      |                                                                                                                                                                                                                                                                                                                                                                                                      |
|---|--------|------------------------------------------------------------------------------------------------------------------------------------------------------------------------------------------------------------------------------------------------------------------------------------------------------------------------------------------------------------------------------------------------------|------------------------------------------------------------------------------------------------------------------------------------------------------------------------------------------------------------------------------------------------------------------------------------------------------------------------------------------------------------------------------------------------------|
|   |        | network connection and equipment debugging between the doctor's console and the patient's surgical platform. After the the correct connection and conditions of all the subsystem of the telesurgery, all the display screens will be turn off, and the patient will be taken to the operation room for the surgery. After the patient is anesthetized, all display screens will be turned on again. | network connection and equipment debugging between the doctor's console and the patient's surgical platform. After the the correct connection and conditions of all the subsystem of the telesurgery, all the display screens will be turn off, and the patient will be taken to the operation room for the surgery. After the patient is anesthetized, all display screens will be turned on again. |
| 5 | Header | Version number: V1.0
Date: September 25th, 2023                                                                                                                                                                                                                                                                                                                                                   | Version number: V2.0
Date: December 8th, 2023                                                                                                                                                                                                                                                                                                                                                     |

---

---

## LIST OF ABBREVIATIONS

| Abbreviation  | Definition                                    |
|---------------|-----------------------------------------------|
| CFDA          | Chinese Food and Drug Administration          |
| REC           | Research Ethics committee                     |
| CRF           | Case report form                              |
| ICF           | Informed Consent Form                         |
| QoR-15 Score  | Quality of recovery 15 items score            |
| EPIC-26 Score | Expanded Prostate Cancer Index Composite-26   |
| NASA          | National Aeronautics and Space Administration |
| ICF           | informed consent form                         |
| ISF           | Investigator Site File                        |
| CT            | Computer tomography                           |
| MR            | magnetic resonance tomography                 |
| ICU           | Intensive Care Unit                           |

## **1. INTRODUCTION**

### **1.1 Development of Telesurgery**

Surgical technology has undergone significant advancements in recent years, progressing from its inception as open surgery to its large-scale implementation of minimally invasive endoscopic surgery and the present stage of minimally invasive endoscopic robot surgery, which is rapidly gaining popularity. Surgical robots have been applied in clinics for more than 20 years, with widespread adoption and positive outcomes. Compared to traditional endoscopic surgery, robotic endoscopic surgery has many advantages. Rapid advances in surgical robotics and telecommunication technology have enabled real-time telesurgery, resulting in the direct control of surgical robotic systems by specialists thousands of kilometers away with virtually no operational latency.

### **1.2 Safety and Reliability of the Telesurgery System**

After rigorous and sufficient technical demonstrations and hundreds of animal tests, the safety, reliability and effectiveness of telesurgery have been preliminarily proved. With the assistance of the technical team of the domestic porous endoscopic surgery robot of China, led by the team of Academician [name] of the Chinese People's Liberation Army (PLA) General Hospital, the telesurgery operation network has been built, which covers most of China's territory. In Beijing and Sanya (3000km), an

explorative, small sample, single arm telesurgery clinical trial has been finished in 2023. We performed telesurgical robot-assisted retrocaval ureteral repair and plastic surgery, radical nephrectomy, partial nephrectomy, radical prostatectomy, adrenal tumor resection, and other operations, all of which were successfully completed with a clear visual field, flexible operation of the robotic arm, good outcome, and no obvious signal latency feel. This preliminarily demonstrated the safety and reliability of robotic telesurgery in endoscopic urologic procedures. The present study on telesurgery systems aims to adopt a variety of technologies to ensure the smooth operation of telesurgery and that there is almost no movement latency during the operation, which can ensure the consistency of "hand-eye coordination" and the overall safety and effectiveness of telesurgery.

Telesurgery may mitigate the challenges faced by patients seeking medical treatment in different locations, rectify disparities in medical proficiency, alleviate the uneven distribution of medical resources during emergencies, and foster the provision of innovative medical and health services and the transparent exchange of medical resources. Reducing the disparity in medical resources across various regions, enhancing the capacity of primary medical and health services, and ensuring the equitable distribution of universal benefits are matters of utmost

importance.

## **2. OUTCOMES**

### **2.1 Primary outcome:**

The primary objective of this clinical trial will be to evaluate and validate the safety and efficacy of the telesurgery system in urologic surgery and compare it to local urologic surgery. The success was defined as the surgery being completed effectively as planned, without conversion to other surgical types and significant side injury or delays due to system malfunctions. Telesurgery was considered successful if it could be completed only using the telesurgery system without conversion to local surgery for any reason. The success or failure of each surgery will be jointly confirmed by the remote and local medical teams together.

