### **3.3 Blinding and Unblinding**

The patients will be blinded. Due to the significant differences in appearance between the experimental and control devices, blinding the researchers will not be possible. Blinding of the patients will be broken until this trial is finished.

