#### **3.4.2 Structure of the telesurgery system and protective measures**

The telesurgery system mainly consists of three subsystems: a surgical robotic subsystem, a telecommunications subsystem, and a teleconference subsystem. The robotic subsystem will consist of a main surgeon console

in the first surgeon's hospital or laboratory and a patient cart in the operation room of the patients' hospital. For safety purposes, a backup surgeon console will be positioned on the patient side in the operating room. In the event of a malfunction with the telesurgery system, the surgeon will take control of the surgery and complete the subsequent types. The telecommunication subsystem will consist of the router and communication line, which will be provided by the network operator. The teleconference subsystem, which can transmit the audio and visual input of the first surgeon and operating room, will be used for communication between the first surgeon and the assistant. The video documentation of all telesurgery procedures will be recorded by the teleconference subsystem. The video documentation of local surgery will also be recorded.

The status of the telesurgery system for the telesurgery group will be monitored by the technique group.

As a protective measure to ensure the safety of the telesurgery, the robotic subsystem has been updated. When the network latency is  $> 200$  ms, the patient cart will stop working, and the telesurgery technique team will inspect and repair the mechanical malfunction of the system. Due to the prolonged duration required to rectify the issues, the surgeon

positioned at the patient's side will take control of the surgery using the backup console and proceed with the remaining surgical steps.

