### **3.5 Standard Follow-up for Patients and the Medical Team**

Patients and medical team members will be followed up by the follow-up team of each center for this trial. Patients will be followed up three times, including at baseline (before the surgery), and 4 and 6 weeks after the surgery. The task load of the surgeon, first assistant, and instrument nurse will be measured immediately after the surgery. For telesurgery, the task load will be measured by the follow-up groups of the surgeon and patient sides together. Patients will continue to receive routine clinical follow-ups, and secondary outcomes will be measured up to 48 weeks.

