### **13.2 Procedures for Recording and Reporting Serious Adverse Events**

All SAEs will be recorded in the medical records and the CRF.

SAEs will also be reported to the chief investigator within 1 hour. A SAE analysis meeting including the technique and surgeon group will review and analyze the SAEs as soon as possible. The video of the surgery and the telesurgery monitoring data will be reviewed to determine the cause of the SAE.

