## **4 Outcomes**

### **4.1 Primary outcome:**

The primary objective of this clinical trial will be to evaluate and validate the safety and efficacy of the telesurgery system in urologic surgery and compare it to local urologic surgery. The success was defined as the surgery being completed effectively as planned, without conversion to other surgical types and significant side injury or delays due to system malfunctions. Telesurgery was considered successful if it could be completed only using the telesurgery system without conversion to local surgery for any reason. The success or failure of each surgery will be jointly confirmed by the remote and local medical teams together.

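### Surgical success is confirmed by unblinded teams, with no stated procedure for control cases and no thresholds for its judgement terms; at 34 per arm one classification can change the conclusion

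*Combined protocol and SAP*

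**What the plan says.** **Who decides.** Protocol 2.1 says of the primary outcome: "The success or failure of each surgery will be jointly confirmed by the remote and local medical teams together". SAP 4.1 has the same rule ("jointly confirmed by the remote and local medical teams together"). SAP 5.1 repeats the definition of success but names nobody who confirms it. Protocol 3.3 blinds patients only and says that "blinding the researchers will not be possible".

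**What counts as success.** Protocol 2.1, SAP 4.1 and SAP 5.1 require effective completion of the planned operation "without conversion to other surgical types and significant side injury or delays due to system malfunctions". A telesurgery case must also be finished "without conversion to local surgery for any reason". Protocol 3.6 gives a second wording: all planned steps done, no conversion, and no *obvious* (rather than *significant*) injury. It does not mention delays.

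**Two sides.** A surgeon side and a patient side appear only for telesurgery (protocol 3.4.2, 3.4.4 and 3.5). An example from 3.5 is: "For telesurgery, the task load will be measured by the follow-up groups of the surgeon and patient sides together".

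**What is recorded.** The protocol section 5 table lists success, surgery conversion and instrument malfunction as separate items at the surgery visit. Protocol 2.2.5 records malfunction of the local robot as well as of the telesurgery system. Telesurgery is filmed, and "The video documentation of local surgery will also be recorded". The one review of video and monitoring data that is described is in protocol 13.2: "The video of the surgery and the telesurgery monitoring data will be reviewed to determine the cause of the SAE".

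**Analysis.** SAP 8.3.1 compares the lower 95% limit of the difference in success rates with -10%, by Miettinen-Nurminen or Newcombe-Wilson. Protocol 9.2 and SAP 3.2 plan 34 patients per arm.

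**The concern.** The rule covers every operation but is worded for a two-site procedure. For a local case the reader cannot tell who the second team is, or whether the local team decides alone. The people who confirm know the arm, and several parts of the definition are matters of opinion. For example, the patient cart stops when latency exceeds 200 ms (protocol 3.4.2 and 12.2). Nothing says whether a stop that is repaired without handover to the bedside console counts as a delay.

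Ascertainment that differs by arm shifts the difference in success rates directly. With very few failures expected, one or two classifications may settle the non-inferiority conclusion. A control case called a failure, or a telesurgery event excused, moves the result toward non-inferiority. The opposite classifications move it away.

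**Working it through.** **1. Inputs.** From protocol 9.2, SAP 3.2 and SAP 8.3.1: success 98% in both arms, margin 10 percentage points, one-sided alpha 0.025, power 80%, 31 per arm before dropout and 34 enrolled per arm, interval by Miettinen-Nurminen (MN) or Newcombe-Wilson (NW).

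**2. The plan's own figure.** n = (1.960 + 0.842)² × (2 × 0.98 × 0.02) / 0.10² = 7.849 × 0.0392 / 0.01 = 30.77, so 31 per arm. This reproduces exactly. Dividing by 0.9 gives 34.19, against 34 planned. The formula uses Wald-type (unpooled) variance.

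**3. Lower limits at 34 per arm.** With no failures both methods have a closed form (z² = 3.841):
- MN: k = 2z²/(2n - 1) = 7.683/67 = 0.1147; limit = -k/(1 + k) = -0.1147/1.1147 = -10.29%.
- NW: limit = -z²/(n + z²) = -3.841/37.841 = -10.15%.

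The other rows were found numerically. The probability column is the product of two binomial probabilities with n = 34 and failure rate 0.02.

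| Telesurgery failures | Control failures | MN | NW | Above -10%? | Probability |
|---|---|---|---|---|---|
| 0 | 0 | -10.29% | -10.15% | no | 25.3% |
| 0 | 1 | -7.50% | -7.49% | yes | 17.6% |
| 1 | 0 | -15.05% | -14.92% | no | 17.6% |
| 1 | 1 | -12.48% | -12.22% | no | 12.2% |
| 1 | 2 | -9.92% | -9.77% | yes | 4.1% |
| 2 | 3 | -11.74% | -11.48% | no | 0.3% |
| 2 | 4 | -9.25% | -9.11% | yes | below 0.1% |

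**4. How often one label matters (98% in both arms).**
- One extra control failure turns a miss into a pass from 0 vs 0, 1 vs 1 and 2 vs 3: 25.3 + 12.2 + 0.3 = 37.8%.
- One control failure fewer turns a pass into a miss from 0 vs 1 and 1 vs 2: 17.6 + 4.1 = 21.7%.
- The two sets do not overlap, so one control label changes the conclusion in 37.8 + 21.7 = 59.5% of outcomes.
- One telesurgery failure relabelled as a success turns a miss into a pass in 13.9% of outcomes, mainly from 1 vs 1 to 0 vs 1.

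MN and NW give the same probabilities.

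**5. If only 31 per arm are analysed.** 0 vs 0 gives -11.19% (MN) and -11.03% (NW), a miss. 0 vs 1 gives -8.15% and -8.11%, a pass. The two control-label probabilities become 32.3% and 18.8%.

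**6. How much is due to the interval.** Under a Wald interval, which matches the sample-size formula, 0 vs 0 passes. A control label then changes the conclusion in about 1.7% of outcomes (1.4% + 0.3%). The SAP does not name that interval.

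**The case against.** - **The control arm may have a workable rule.** A reader might infer that control cases cannot be confirmed as written because local surgery has no remote team. The documents do not say so. Local operations are filmed, so an off-site team could take part. What stands is that the procedure for control cases is not stated.
- **The main failure route is factual.** Conversion is a recordable event, and the rule that any conversion to local surgery is a failure works against telesurgery. This narrows the room for opinion, but injury, delay and effectiveness remain open.
- **No bias is shown.** It is tempting to conclude that the rule favours telesurgery. Nothing in the documents shows that control cases would be judged more strictly, so the direction is unknown.
- **The records largely exist.** Conversion, malfunction and operative details are already collected, and protocol 13.2 gives one use of the video without excluding others. This is correct and makes the fix cheap. No text, however, makes these records determine the primary outcome.
- **A robustness analysis is mentioned.** SAP 8.3.1 allows a tipping analysis, but it is optional, and what is to be tipped is not specified.
- **The fragility has another source.** Sizing with a Wald-type formula and analysing with score-type limits would leave the result fragile even with perfect ascertainment. This is a separate defect, and while it lasts each classification carries more weight.

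**Conclusion.** The point holds as a gap in ascertainment. Confirmation is unblinded, it is not specified for control cases, and it rests on terms without thresholds that are worded differently in protocol 3.6. This is a risk of differential classification, not evidence that it will occur or which arm it would favour.

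A reader might also infer that one relabelled control case always decides the trial. It does so in about 60% of outcomes at the design rates. At 1 vs 0, or at 0 vs 2 or more, one control label changes nothing. Nor is the result without failures a 50% event: 0.98^34 = 50.3% is the chance of no failure in one arm, and for both arms it is 0.98^68 = 25.3%, still the single most likely result.

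These figures assume 98% true success in both arms, independent cases, all 34 per arm analysed, and one of the two interval methods named in the SAP.

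**What to change.** 1. Reconcile protocol 2.1, protocol 3.6, SAP 4.1 and SAP 5.1 into one definition of success, and apply one confirmation rule to both arms.
2. Derive success or failure from items recorded at the surgery visit in both arms: conversion, instrument malfunction and injury in the operative record. For telesurgery, add the system monitoring log.
3. State which recorded entries count as significant injury and which as delay due to system malfunction.
4. Have the same theatre roles sign the form in each arm, for example the first surgeon and the first assistant. A recorded qualifying event counts as failure whatever the team's opinion.
5. Add a sensitivity analysis of the primary outcome that counts every disagreement between record and team as a failure in the telesurgery arm and as a success in the control arm.

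The cost is one CRF page, wording in both documents and a little analysis work, with no new staff. Because the signatories remain unblinded, this limits the risk of bias without removing it. The mismatch between sample-size formula and interval needs its own correction.

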### **2.2 Secondary outcomes:**

The secondary outcomes of this study will be to investigate differences between telesurgery and local surgery in terms of complications and early recovery quality, physical functioning, early oncological outcomes, task load of the medical team, adverse events, and status or malfunction of the local surgery robotic or telesurgery system.

#### **2.2.1 Early recovery**

The following tools will be used to measure the early recovery:

1. Overall functional recovery: Quality of recovery 15-item score (QoR-

15 score) at baseline (preoperative), 4 weeks, and 6 weeks.

2. Overall functional recovery for prostate cancer patients: Expanded Prostate Cancer Index Composite-26 (EPIC-26 score) at baseline (preoperative), 4 weeks, and 6 weeks.

3. Physical activity: 30-second chair-to-stand test (number of times the patient can stand from sitting in a 30-second interval) at baseline (preoperative), 4 weeks, and 6 weeks.

### **2.2.2 Perioperative morbidity**

To assess perioperative morbidity, the following clinical data will be collected:

1. Surgery-associated factors: intraoperative blood loss, operative time, and warm ischemia time (for partial nephrectomy).
2. Complications and adverse events: Adverse events will be recorded using the Clavien-Dindo classification at 4 weeks and 6 weeks postoperatively.
3. Postoperative hospitalization days.
4. Length of days in critical care.
5. Reoperational intervention.
6. Readmission to the hospital: Readmission to the hospital for any reason will be recorded, and the surgery-associated condition will be systemically reviewed.

7. Intra- and postoperative blood transfusion rates.

8. Mortality rate.

### **2.2.3 Oncological outcomes**

To assess the oncological outcomes, the following pathological data will be collected:

1. Positive margin rate in the pathological specimen according to the pathology report from two blinded pathologists in each hospital.
2. Pathological type of the tumor;
3. The Gleason score and number of retrieved lymph nodes in the pathological specimen for prostatectomy with lymph node dissection only.

